### Special management of hypertension related to targeted therapy

**Situations of hypertension caused by targeted drug therapy:** Vascular endothelial growth factor (VEGF) signaling pathway inhibitors such as Bevacizumab and Sorafenib can cause hypertension or exacerbate pre-existing hypertension. Its main mechanisms of action may include: decreased secretion of NO/PGI2 from endothelial cells/platelets, abnormal vascular density (small vessels and capillaries), vascular stiffness, and dysfunction of endothelin. Sunitinib may also lead to a decrease in left ventricular ejection fraction (LVEF).

**Monitoring and management of this type of hypertension:** Blood pressure should be monitored weekly for 6 weeks prior to the initiation of targeted drug therapy. Once hypertension occurs, the following standard treatment medications may be administered: angiotensin II receptor (AT1) blockers, β-blockers, diuretics, angiotensin-converting enzyme inhibitors (ACEI), or a combination of the aforementioned medications.

**Reference for the treatment of hypertension caused by similar drugs:** Hypertension after sorafenib treatment generally occurs 1 to 2 weeks after medication initiation, and can often be managed with routine antihypertensive treatment. For hypertension that is difficult to control, it can generally be alleviated by reducing the dosage of the targeted drug or discontinuing it.

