Safety study results: A total of 5 patients experienced DLT in this study, including 1 case in the 0.2g dose group, 1 case in the 0.3g dose group, and 3 cases in the 0.4g dose group. During the study period of single and multiple administrations, a total of 20 cases (80.0%) experienced adverse reactions (ADR). The incidence of ADR during the single administration phase was 36.0% (9/25), while the incidence of ADR during the multiple administration phase was 86.4% (19/22). Ranked by incidence, the most common adverse reactions were hand-foot syndrome (12 cases, 48.0%), diarrhea (8 cases, 32.0%), rash (6 cases, 24.0%), alopecia (5 cases, 20.0%), nail pigmentation (5 cases, 20.0%), and hypertension (5 cases, 20.0%). According to the classification by system organ, the 'gastrointestinal system' is the most common adverse reaction, with a total of 16 out of 25 patients (64.0%) experiencing 'gastrointestinal system' related adverse reactions. The main manifestations include diarrhea (8 cases, 32.0%), stomatitis (4 cases, 16.0%), reduced food intake (3 cases, 12.0%), nausea (2 cases, 8.0%), abdominal distension (2 cases, 8.0%), constipation (2 cases, 8.0%), and abdominal pain (2 cases, 8.0%). Fifteen patients (60.0%) experienced 'skin and subcutaneous tissue' related adverse reactions. The main 'skin and subcutaneous tissue' adverse reactions were hand-foot syndrome (12 cases, 48.0%), rash (6 cases, 24.0%), alopecia (5 cases, 20.0%), and nail pigmentation (5 cases, 20.0%), among others.

PK studies indicate that a single administration of donafenib , within the dose range of 0.1 to 0.4 g, results in an increase in the AUC _0-t_ and C _max_ of the parent drug in subjects as the administration dose increases, with the increase of the parent drug being generally consistent with the proportional increase in dose; the PK parameters of donafenib exhibit considerable inter-subject variability. donafenib was administered continuously, twice daily (Bid), for 28 days. During days 7 to 14 of administration, the plasma concentrations of donafenib and its metabolites reached a steady state. The ratio of the AUC _0-12h_ of donafenib on day 28 to that on day 1 (accumulation ratio) was 2.94 to 7.75, indicating a degree of accumulation. Within the dose range of 0.1 to 0.4 g, the AUC _0-12h,ss_ and C _max_ of donafenib did not show significant changes with increasing doses. A high-fat diet had little effect on the PK parameters of donafenib .

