## Screening Period (-14 days to 0 days)

1. The examinations in the screening items of this phase are part of the routine clinical treatment process. The results of examinations conducted at this research center prior to the patient's signing of the informed consent form (within 14 days before screening assessment) can be used to evaluate the eligibility of subjects for inclusion and serve as the baseline for enrolled subjects;
2. Demographic data: including date of birth, gender, race/ethnicity;
3. History of tumor and treatment: date of tumor diagnosis, start/end dates of previous treatment regimens, best treatment assessment, date of disease progression; history of radiotherapy must include start/end dates and the site of radiotherapy; Any significant previous procedures (such as gastroscopy, puncture biopsy, and other diagnostic or therapeutic invasive procedures) must be recorded in the CRF, including start and end dates, name of the procedure, and site; Date of liver cancer radical surgery, maximum diameter of the tumor before and during surgery, number of nodules, presence of PVTT and its classification (for PVTT classification, see [Appendix Six](#附录九) ), as well as postoperative pathological results, including pathological diagnosis, MVI, satellite lesions, etc.;
4. Medical history/treatment history: Collect all past medical history and treatment history, excluding this indication, that began before signing the ICF and is considered relevant to this study;
5. Alcohol history, smoking history;
6. ECOG PS score: It is recommended that the ECOG PS evaluation be conducted by the same investigator throughout the study period, see [Appendix Five](#附录七) ;
7. Child-Pugh score and BCLC staging (Child-Pugh score see [Appendix Four](#附录六) );
8. Safety data:

- Physical examination: including head, eyes, ears, nose, throat, neck, heart, chest (including lungs), abdomen, limbs, skin, lymph nodes, nervous system, and general condition of the subjects, as well as height and weight measurements; subjects should wear indoor clothing and remove shoes when measuring weight;
- Vital signs examination: temperature, respiration, blood pressure, and heart rate; Blood pressure and heart rate should be measured after the patient rests in a sitting position for 5 minutes;
- Complete blood count: red blood cell count, hemoglobin, hematocrit, white blood cell count and differential (neutrophils, lymphocytes, eosinophils, monocytes, basophils), and platelet count;

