## Donafenib monotherapy phase (Day 1 to Day 3~7)

After subjects are screened and qualified, they will first enter the donafenib monotherapy phase and will begin taking donafenib within 24 hours of enrollment, with the day of taking donafenib recorded as D1. The administration dose is 200 mg bid daily, continuing for 3~7 days.

All data obtained from these evaluations must be supported by the patient's original records. The CRF does not serve as original records.

1. Safety checks must be completed before each medication administration, and blood collection must not occur earlier than 3 days prior to medication administration. Results must be determined by the investigator to meet the criteria for continuing medication before treatment can begin. The items collected are the same as those in the screening phase, except for the following items:

- A limited physical examination based on symptoms should be conducted; height measurement is not necessary.
- If blood routine, blood biochemistry, urine routine, stool routine, coagulation function, electrocardiogram examination, and vital signs are performed within 3 days prior to the first administration, there is no need to repeat the corresponding examinations on Day 1 of the donafenib monotherapy period.
- Virology testing does not need to be repeated on Day 1 of the donafenib monotherapy period; thereafter, HBV DNA should only be tested in known HBV-positive patients and HCV RNA in known HCV-positive patients.
- Thyroid function does not need to be rechecked on Day 1 of the donafenib monotherapy period; if there are clinically significant changes in thyroid function during treatment, it is recommended to consult endocrinology and rule out pituitary dysfunction.
- Cardiac color Doppler ultrasound does not need to be repeated on day 1 of the donafenib monotherapy period; thereafter, it should only be performed if the subject has clinical indications (such as ECG abnormalities, chest tightness, cyanosis, dyspnea, etc.) or if the investigator deems it necessary.
- Pregnancy tests do not need to be repeated on day 1 of the donafenib monotherapy period; thereafter, a urine pregnancy test can be conducted, and if the result is positive, a blood pregnancy test should be performed.

1. AFP testing: does not need to be repeated on day 1 of the donafenib monotherapy period.

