2. ECOG PS score collection. If it is conducted within 3 days prior to the first administration, there is no need to repeat the collection on day 1 of the monotherapy period with donafenib ;
3. Investigational drug treatment (donafenib monotherapy);
4. Dispense the treatment drug for the donafenib monotherapy period;
5. Conduct DLT observation after administration: applicable only to patients entering the safety induction phase, i.e., the first 6 patients enrolled;
6. Collect concomitant medication/treatment;
7. Collect adverse events: the adverse events of subjects must be closely monitored throughout the entire research process.
   1. Combination treatment period (the first use of Sintilimab is designated as CIDI, with visits every 3 weeks, time window ±3 days)

After 3-7 days of monotherapy with donafenib , if the subjects are well-tolerated to donafenib during the monotherapy period as assessed by the investigator, subsequent subjects may receive intravenous infusion treatment with Sintilimab injection, and begin approximately 1 day of HAIC treatment on the same day or the day after the infusion of Sintilimab.

All visits during the combination treatment period will be scheduled according to the appropriate calendar days starting from the combination treatment period C1D1 (the day of first use of Sintilimab), with a treatment cycle of every 3 weeks (the length of the 3-week cycle is fixed, regardless of whether the investigational drug is paused). An allowable visit time window of ±3 days is permitted. If at any time during the study the treatment with the investigational drug is paused, all study visits, safety, and efficacy assessments should continue according to the evaluation schedule based on the appropriate calendar days from the combination treatment period C1D1. All data obtained from these assessments must be supported by the original records of the patient. The CRF does not serve as the original record.

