**Attachment 1 Trial Flowchart**

| **Research Phase** | **Screening Period (D)** | **donafenib Monotherapy Period**  **(Duration 3~7 days)** | **Combination Therapy Period**  **(Every 3 weeks constitutes one treatment cycle)** | | | | **End of Treatment** | **Post-Treatment** | | |
| --- | --- | --- | --- | --- | --- | --- | --- | --- | --- | --- |
|  |  |  | **C1D1** | **C2D1** | | **C3D1、C4D1……** | **Confirmation within 7 days after end/discontinuation of treatment** | **Safety follow-up** | **Efficacy Follow-up** | **Survival follow-up** |
|  | **-14 ~ -0** | **D1** | **±3D** | **±3D** | | **±3D** |  | **30±7 days after last administration** | **Every 12 weeks or 24 weeks ±7 days** | **Every 12 weeks**  **±7D** |
| Informed Consent **^1^** | × |  |  |  | |  |  |  |  |  |
| Demographic Information ^2^ | × |  |  |  | |  |  |  |  |  |
| Smoking History, Alcohol Consumption History | × |  |  |  | |  |  |  |  |  |
| Past Medical History and Treatment History | × |  |  |  | |  |  |  |  |  |
| Previous tumor history and treatment history, including postoperative pathology | × |  |  |  | |  |  |  |  |  |
| Physical examination **^3^** | × | × |  | × | | × | × | × |  |  |
| Height measurement **^4^** | × |  |  |  | |  |  |  |  |  |
| Weight measurement **^5^** | × | × |  | × | | × | × | × |  |  |
| ECOG PS score **^6^** | × | × |  | × | | × | × | × | × |  |
| Vital signs **^7^** | × | × | × | × | | × | × | × |  |  |
| Child-Pugh score | × |  |  | × | | × | × |  |  |  |
| BCLC liver cancer staging | × |  |  |  | |  |  |  |  |  |
| Complete blood count, blood biochemistry, urinalysis, coagulation function **^8^** | × | × |  | × | | × | × | × |  |  |
| Fecal occult blood | × | Only performed when there are clinical indications or deemed necessary by the investigator | | | | | | |  |  |
| Pregnancy test **^9^** | × |  |  |  | |  | × |  |  |  |
| Cardiac ultrasound **^10^** | × | Only performed when there are clinical indications or deemed necessary by the investigator | | | | | | |  |  |
| 12-lead electrocardiogram | × | × |  | × | | × | × | × |  |  |
| Virology testing **^11^** | × |  |  | | Known HBV positive patients should be tested for HBV DNA,  HCV RNA testing for known HCV positive patients; | | | |  |  |
| Thyroid function **^12^** | × |  |  | | × | × | × | × |  |  |
| AFP **^13^** | × |  |  | × | | × | × | × |  |  |
| Tumor assessment (CT/MRI) **^14^** | × |  | Once every 6 weeks ± 3 days (relative to C1D1) | | | | × |  | × |  |

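### Section 8.3.2 sets a pre-treatment blood pressure rule that screening cannot hold, and the flowchart leaves 18 to 24 days after C1D1 with no scheduled reading

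*Protocol*

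**What the plan says.** Section 8.3.2, on hypertension related to targeted therapy, gives one monitoring instruction with a frequency: "Blood pressure should be monitored weekly for 6 weeks prior to the initiation of targeted drug therapy". It then says of sorafenib, cited as a similar drug, that hypertension "generally occurs 1 to 2 weeks after medication initiation". Its staging list starts antihypertensive drugs from 140/90 mmHg and calls for two drugs from 160/100 mmHg.

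The visit schedule is set elsewhere. Section 6.1 runs screening from day -14 to day 0 and accepts results obtained at the centre "within 14 days before screening assessment". Under section 6.2 a subject "will begin taking donafenib within 24 hours of enrollment", that day is D1, and monotherapy lasts 3 to 7 days. Section 6.3 counts the combination period from the first sintilimab infusion (C1D1), "with visits every 3 weeks, time window ±3 days".

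The flowchart (Attachment 1) marks vital signs at screening, D1, C1D1, C2D1, each later cycle, end of treatment and safety follow-up. Its note 7 lists blood pressure among the vital signs. There is no separate blood pressure row.

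**The concern.** The only stated frequency for blood pressure applies to a period that the trial does not contain. A site following section 8.3.2 has an instruction it cannot carry out. A site following the flowchart takes no weekly reading before or during donafenib.

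This matters because of timing. The section places the usual onset in the second week of treatment, and the schedule is nearly empty there. Donafenib is a deuterated form of sorafenib (section 1.3), and its first clinical study lists hypertension as an adverse reaction in 5 of 25 patients (section 1.3.2.1). The staged management in section 8.3.2 can begin only once a reading has been taken. Raised pressure without symptoms that begins after C1D1 may go unseen until C2D1.

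**Working it through.** **Inputs.** Pre-treatment rule: weekly for 6 weeks (8.3.2). Screening: 14 days; prior results accepted: up to 14 more days (6.1). Donafenib start: within 24 hours of enrolment, first dose day = D1; monotherapy 3 to 7 days (6.2). Cycle: 21 days from C1D1, window ±3 days (6.3). Reading times: vital-signs row of the flowchart. Onset: 1 to 2 weeks after start, for sorafenib (8.3.2).

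**1. Can the rule be met as written?**
- The plan's figure: 6 × 7 = 42 days. On the most lenient count, six readings 7 days apart span 5 × 7 = 35 days.
- Available: 14 days, or 14 + 14 = 28 on the most generous use of prior results.
- Shortfall on the lenient count: 35 − 14 = 21 days, or 35 − 28 = 7 days. On the full 6 weeks: 42 − 14 = 28 days, or 42 − 28 = 14 days.
- Weekly readings that fit: 3 in 14 days (days -14, -7, 0) and 5 in 28 days. Six never fit.

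**2. When are the on-treatment readings?**
- C1D1 = D1 + 3 to 7 days = D4 to D8.
- C2D1 = C1D1 + 21 ± 3 days: earliest 4 + 18 = D22, latest 8 + 24 = D32.
- Gap from C1D1 to C2D1: 21 − 3 = 18 to 21 + 3 = 24 days.
- C3D1 = C1D1 + 42 ± 3 days: 4 + 39 = D43 to 8 + 45 = D53, after week 6 ends on D42.

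The vital-signs check after the first infusion (8.4.1) falls on C1D1 and does not shorten the gap.

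**3. What falls in the cited onset period?** Seven to 14 days after the first dose is D8 to D15. C1D1 reaches it only at the 7-day extreme (D8). The earliest C2D1, D22, lies beyond it. So there is one scheduled reading if C1D1 is on D8 and otherwise none.

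**4. Sensitivity.** The flowchart also prints ±3D under C1D1. If that is applied, C1D1 falls on D1 to D11 and C2D1 on D19 to D35. The gap is still 18 to 24 days, and the onset period still holds at most one reading.

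**5. Weeks without a reading in the first six (D1 to D42), using the D4 to D8 range.**
- C1D1 on D4 to D7: D1 and C1D1 cover week 1, and C2D1 covers week 4 or 5. Uncovered: 6 − 2 = 4 weeks.
- C1D1 on D8: D1 covers week 1, C1D1 week 2, and C2D1 week 4 or 5. Uncovered: 6 − 3 = 3 weeks.

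**The case against.** The strongest reply is that section 8.3.2 is general guidance on a drug class, worded as advice, while section 6 and the flowchart set the visits and work as they stand. Nothing in eligibility makes six weeks of readings a condition for starting donafenib, so no patient is blocked. That is right. It limits the consequence but does not make the instruction feasible.

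A second reply is that the two halves rest on different readings. Taken literally, the sentence asks for nothing on treatment, so a schedule of readings every 3 weeks does not contradict it. If the first 6 weeks of therapy were meant, the impossibility disappears and only a table row is missing. This is fair. The on-treatment meaning is an inference that the text does not show. Under either reading, however, section 8.3.2 and the flowchart do not fit together, and the gap sits over the onset period that the section cites.

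Third, there are safeguards. Adverse events are followed closely throughout, unscheduled readings are not forbidden, uncontrolled hypertension is excluded at entry, and section 8.3.2 asks for monitoring from the prehypertensive range upward. These help, but none schedules a reading at a stated interval for a patient without symptoms.

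Three stronger inferences are tempting and not supported:
- **A dose-limiting toxicity would be missed.** The blood pressure criterion in section 3.4 needs at least two readings 24 hours apart, and the gap lies within the observation window. Event-triggered readings remain possible, and the dose change also needs at least two cases judged solely related to donafenib. No effect on that decision is shown.
- **The second week never has a reading.** With the first dose as D1, C1D1 can fall on D8.
- **The 5 of 25 rate forecasts cases among the 30 patients.** That study mixed doses and tumour types, and the protocol gives no onset times. The rate measures neither the gap nor any harm.

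**Conclusion.** The point holds as a safety-monitoring inconsistency. The pre-treatment rule falls short by at least 7 days on the most generous count and by 28 days on the plainest one (42 against 14). The flowchart leaves 18 to 24 days after C1D1 with no scheduled reading, and at most one scheduled reading falls in the cited onset period. These figures rest only on the protocol's own calendar, with the first dose as D1 and later visits counted from C1D1. Their relevance to donafenib assumes an onset similar to sorafenib's, which the section itself uses as its reference. ORR is unaffected.

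**What to change.** Reword the sentence in section 8.3.2 to require weekly blood pressure during the first 6 weeks of donafenib, with the baseline taken from screening and D1. The sponsor should confirm that this was the intent. Add a matching blood pressure row to the flowchart, and allow home or local cuff readings in weeks without a visit.

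The cost is one phrase, one row and about 3 to 4 extra cuff readings per patient. Over 30 patients that is 3 × 30 = 90 to 4 × 30 = 120 readings. No extra visit or invasive procedure is needed.

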**Optimized choice of drugs for hypertension caused by targeted therapy (non-hepatic metabolism):**

- Valsartan (Diovan), 80~320 mg once daily (Qd);
- Atenolol (Tenormin), 50~100 mg Qd;
- HCTZ (Hydrochlorothiazide), 12.5~100 mg Qd;
- Telmisartan (Micardis), 20~80 mg Qd;
- For patients with difficult-to-control blood pressure: Amlodipine (Norvasc), 2.5~10 mg Qd.

**Clinical staging of hypertension and conventional management methods for each stage**

- **Prehypertension:** (120~139/80~89 mmHg, or systolic blood pressure of 120~139 mmHg) no indication for antihypertensive medication, only monitor blood pressure.
- **Stage 1 hypertension:** (140~159/90~99 mmHg, or systolic blood pressure of 140~159 mmHg) initiate antihypertensive medication while monitoring blood pressure; Most commonly, thiazide diuretics are used; consideration may also be given to ACE inhibitors, angiotensin receptor blockers, β-blockers, and calcium channel blockers. If blood pressure control is inadequate, the combination of two antihypertensive agents may be considered.
- **Stage 2 hypertension:** (160~179/100~109 mmHg, or systolic blood pressure ≥ 160~179 mmHg) requires the combination of two medications (usually a thiazide diuretic with either an ACE inhibitor or a β-blocker or a calcium channel blocker); monitor blood pressure.
- **Stage 3 hypertension:** (≥ 180/110 mmHg, or systolic blood pressure ≥ 180 mmHg) requires the combination of two medications (usually a thiazide diuretic with either an ACE inhibitor or a β-blocker or a calcium channel blocker); Closely monitor blood pressure, assess other risk factors (such as target organ damage, diabetes, and accompanying clinical symptoms), and take appropriate measures.
- **Hypertensive crisis:** Refers to a severe clinical condition where blood pressure is excessively elevated, with diastolic pressure exceeding 16.0~17.3 kPa (120~130 mmHg). There is currently no unified classification method domestically and internationally. Recently, from a clinical treatment perspective, it has been divided into two types:
- Hypertensive emergency with diastolic pressure > 16.0 kPa (120 mmHg), accompanied by acute or progressive target organ damage, such as cerebral infarction, intracranial or subarachnoid hemorrhage, hypertensive encephalopathy, etc., among which progressive or acute hypertension based on chronic primary hypertension is the most common (approximately 40%~50%).
- Hypertensive emergency, diastolic pressure > 16.0 kPa (120 mmHg) without or only mild organ damage. Use sodium nitroprusside or nifedipine for rapid blood pressure reduction, diazepam and phenobarbital to stop seizures, furosemide and mannitol for dehydration, sodium excretion, and lowering intracranial pressure.

**Principles of using conventional antihypertensive drugs:** Currently, the common combinations for hypertension treatment involve ACE inhibitors (or AT1 antagonists) with diuretics; calcium channel blockers with β-blockers; ACE inhibitors with calcium channel blockers; diuretics with β-blockers; α-blockers with β-blockers. The following is an overview of the commonly used antihypertensive medications in clinical practice.

- **Diuretics:** Diuretics are primarily used for mild to moderate hypertension, especially in elderly patients with hypertension or concurrent heart failure. They are contraindicated in patients with gout and should be used with caution in patients with diabetes and hyperlipidemia. Low doses can avoid adverse reactions such as hypokalemia, impaired glucose tolerance, and arrhythmias. Hydrochlorothiazide 12.5 mg can be chosen, 1-2 times daily; indapamide 1.25-2.5 mg, once daily. Furosemide is only used in cases of concurrent renal failure.
- **Beta-blockers:** Beta-blockers are primarily used for mild to moderate hypertension, especially in young and middle-aged patients with a resting heart rate greater than 80 beats per minute or those with concomitant angina. Contraindicated in patients with cardiac conduction block, asthma, chronic obstructive pulmonary disease, and peripheral vascular disease. Use with caution in insulin-dependent diabetes mellitus patients. Options include Metoprolol 50 mg, 1-2 times daily; Atenolol 25 mg, 1-2 times daily; Bisoprolol 2.5-5 mg, once daily; and Betaloc 5-10 mg, once daily. Beta-blockers can be used for heart failure, but their usage differs completely from that for lowering blood pressure, and caution should be exercised.
- **Calcium channel blockers:** Calcium channel blockers can be used for various degrees of hypertension, especially in elderly patients with hypertension or stable angina. Non-dihydropyridine calcium channel blockers are contraindicated in patients with cardiac conduction block and heart failure. Short-acting dihydropyridine calcium channel blockers are contraindicated in unstable angina and acute myocardial infarction. Long-acting formulations are preferred, such as felodipine sustained-release tablets 5~10 mg, once daily; nifedipine controlled-release tablets 30 mg, once daily; amlodipine 5~10 mg, once daily; lercanidipine 4~6 mg, once daily; verapamil sustained-release tablets 120~240 mg, once daily. Under normal circumstances, nifedipine or nicardipine ordinary tablets 10 mg may also be used, 2 to 3 times daily. Use nifedipine rapid-release capsules with caution.
- **Angiotensin-converting enzyme inhibitors:** Angiotensin-converting enzyme inhibitors are mainly used for patients with hypertension combined with diabetes, or those with heart failure or renal impairment with proteinuria. Contraindicated in patients with pregnancy, renal artery stenosis, or renal failure (serum creatinine > 265 μmol/L or 3 mg/dL). The following formulations may be chosen: Captopril 12.5~25 mg, 2~3 times daily; Enalapril 10~20 mg, 1~2 times daily; Perindopril 4~8 mg, once daily; Silapril 2.5~5 mg, once daily; Benazepril 10~20 mg, once daily; Ramipril 2.5~5 mg, once daily; Lisinopril 20~40 mg, once daily.
- **Angiotensin II receptor antagonists:** AT1 antagonists, such as Losartan 50~100 mg, once daily, Valsartan 80~160 mg, once daily. The applicable and contraindicated populations are the same as for ACEI, currently mainly used for patients who develop a dry cough after ACEI treatment.

